### Data management and confidentiality

All participants will be identified by a Participant ID which is a code assigned to them when they enroll in the study. The only document which will contain both their name and their ID will be the Informed Consent Form. Signed informed consent forms will be kept in a locked cupboard in the Chief Medical Health Officer’s office in each district. After participants sign informed consent, all further forms will only contain their ID, not their name. A master sheet with all participant names and the corresponding IDs will be saved on a password-protected sheet which is only accessible by the research associates, project manager and PIs. Data entry will be done by research associates of the project.

### Potential harms

Any untoward medical occurrence, and/or (b) serious adverse events: suicide attempt, death due to suicide, death due to other causes, violence experienced by the participant, violence experienced by any other family member, and unplanned hospitalization will be reported. Although suicide attempt and death by suicides are outcome variables, we will also monitor them as if they are serious adverse events to ensure that the intervention is not associated with increase in suicide/attempted suicides.

### Protocol amendments

In the event of significant protocol modifications, our research team will promptly communicate changes in eligibility criteria, outcomes, analyses, and other vital aspects to the Indian Law Society Ethical Review Board in India, CTRI trial registry and Utrecht University, Netherlands Ethical Approval Board.

### Progression criteria

To determine if this study will proceed to a randomized controlled trial, we have developed progression criteria based on recommendations put forth by Mellor et al. (2023).
^
37
^ The progression criteria is focused on assessing the feasibility of the study design and the feasibility and appropriateness of the intervention, indicated in
Table 2 below.

**Table 2. T2:** Progression criteria for primary outcomes.

Outcome	Progression criteria
Feasibility of participant recruitment	Minimum recruitment rate of 50% of eligible participants
Feasibility of intervention design	• Retention of participants: <30% loss to follow up at 6-month data collection • Retention of CHOs: <20% of CHOs discontinue delivery of CASP sessions
Intervention implementation	Delivery of the intervention judged as highly feasible and acceptable by health workers and participants through qualitative data

These criteria have been selected considering practical limitations and contextual factors that may challenge the feasibility of integrating CASP into the existing health system, for e.g. lack of government resources to incentivize new tasks for health workers, significant distances to be travelled between facilities and participant homes (without adequate travel compensation) for CHOs, and stigma around suicide. As this is the first integration of CASP within the existing health system, one key focus of this study is to assess the impact of practical and contextual limitations and identify where and how we can adapt the study processes to better suit low resourced public health settings (where the scope for scale-up is largest).

Red Amber Green traffic light approach
^
37
^: Keeping the abovementioned contextual factors in mind, if after the completion of the pilot study the progression criteria are not met by more than 20% as per quantitative data, and the study is not found to be feasible as per qualitative data, this will be considered under the Red threshold and further exploration of this approach will not be considered. If the criteria are within a 20% range (lower than indicated), this will be considered within the Amber threshold and a reassessment will be carried out by the steering committee and relevant stakeholders, and appropriate adaptations of the intervention and trial processes will be made. If the criteria are met or exceeded by study data, then the intervention will be considered feasible and further assessment in a definitive trial may be explored.

### Dissemination

Dissemination of study findings will be done via the following channels: a) academic publications in peer reviewed, open access journals; b) development and dissemination of an easy-to-understand policy brief that highlights the study’s key findings and recommendations, geared towards policy-makers and stakeholders of the continued implementation or scale-up of CASP within the health system; and c) dissemination meetings within the districts in Chhattisgarh where the research was carried out, as well as among academic networks, healthcare professionals and relevant suicide prevention stakeholders.

### Study status

Participant recruitment and follow-up data collection for the CASP study is ongoing; data collection will conclude in November 2025.

## Discussion

This pilot study evaluates the implementation and preliminary effectiveness of a contact and safety planning (CASP) intervention delivered by trained health workers for suicide prevention in Chhattisgarh, India. While CASP has been previously tested among a refugee population in South India,
^
8
^ this study is the first to adapt and integrate CASP for an at-risk population within the public health system. By assessing the intervention’s feasibility, reach, acceptability, adoption, and early indications of effectiveness and cost, this study seeks to generate critical evidence for suicide prevention within the health system in low-resource settings.

Conducted in collaboration with the Chhattisgarh Department of Health and Family Welfare, CASP aims to address systemic challenges felt within the health system for suicide prevention in Chhattisgarh. For example, in the control districts of Mungeli and Balodabazar, while DMHP staff provide brief follow-ups and counseling for individuals who attempt suicide and present to emergency wards in district health centres, most other districts lack adequate personnel to fulfil these roles. As a result, attempted suicides often go unattended to. Additionally, nurses in emergency wards are not trained to identify and sensitively respond to attempted suicides, which can influence the care provided and medical decision-making in emergency settings.
^
38
^ Training emergency nurses and Community Health Officers (CHOs) as a key link between emergency departments—a common point of contact for individuals at risk—and the community provides a promising pathway to address these gaps.

We anticipate challenges when implementing this study. The unexpected doubling of the CHO trainee pool due to the placement of over 200 additional CHOs in district Health and Wellness Centres poses logistical difficulties for keeping to the study timeline and carrying out supervision and coordination with CHOs. Stigma around suicide within families and communities may hinder follow-ups and which are central to this model. Additionally, the lack of systematic data collection on suicide attempts and follow-ups in control districts complicates the evaluation. To mitigate this, data collectors will conduct weekly visits to engage with primary and community health centres and support in improving the consistency and quality of data collection and reporting at this level.

This study is timely and essential, given the growing global public health burden of suicide, particularly in low- and middle-income countries (LMICs). It addresses critical gaps in the literature regarding effective suicide prevention interventions in community settings and explores barriers and facilitators to implementation in under-resourced contexts.
^
39
^ Furthermore, it provides a practical perspective on the potential of health worker training at multiple levels to enhance suicide prevention efforts, and explores the ability for this programme to be scalable within and by the health system. Findings from this study will contribute to the definitive testing of CASP as a scalable intervention and inform strategies for integrating suicide prevention programs within public health systems in LMICs.

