^ and is recommended by the World Health Organisation (WHO) as an effective intervention to reduce suicides and attempted suicides in the general population.
^
13
^ Safety planning interventions have been found to reduce fatal and non-fatal suicide attempts in a recent meta- analysis
^
9
^ and when tested in conjunction with brief contact among veterans in the US.
^
14
^ Leveraging the public health system to deliver CASP may be a promising solution to address the treatment gap for suicide in Chhattisgarh and similarly low-resourced settings, however, the feasibility and acceptability of a health-systems approach for CASP is yet to be determined.

This study will integrate CASP into the public health system by training non-specialist health workers to identify and follow up with adults who have recently attempted suicide in two districts where the DMHP is not providing any response to suicide attempts (due to personnel shortages). We will train two groups of health workers: (1) nurses in emergency wards of health centres to identify and recruit adults who have attempted suicide from emergency wards, and (2) Community Health Officers (CHOs) at community-based Health and Wellness Centers (HWCs) to deliver the CASP intervention in the community over an 11-week follow-up period.

Follow ups by CHOs will include suicide risk assessments, provision of emotional support and empathetic listening, and collaborative safety planning to identify steps a participant can follow if they are in distress. Steps include identifying symptoms of distress, recognizing coping mechanisms and planning for future use of coping strategies, activating support networks, referrals for professional care and sharing details of the nearest emergency services. The first follow up visit will occur within one week of discharge from a healthcare facility post-attempt, and then continue periodically over the immediate 11-week period afterward.

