### Study design

The CASP intervention will be tested in the form of a 1:1 non-randomized, controlled pilot study. The pilot study will consist of two arms, comparing the CASP intervention in the two districts of Balod and Rajnandgaon against Enhanced Usual Care in the two districts of Mungeli and Balodabazar.

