### Control condition: Enhanced Usual Care (EUC)

In Chhattisgarh, usual care under the DMHP includes a telephonic follow-up, where a social worker or a clinical psychologist at the DMHP clinic provides counselling for an individual who has recently attempted suicide, and invites them to visit the DMHP clinic in person to receive continued support. However, some clinics (such as in as our intervention districts) do not have any existing follow up care for suicide due to staff shortages, and so the CASP pathway will serve as the primary follow-up response in these districts. In the control districts, participants will receive Enhanced Usual Care (EUC). EUC will consist of the usual care provided by the District Mental Health Plan (DMHP) in Balodabazar and Mungeli, which have an active DMHP program staffed by a social worker, a nurse as well as a psychiatric nurse, a clinical psychologist and a Medical Officer (MO) (a medical professional based in primary and community care clinics). DMHP personnel in control districts are trained in telephonic counselling for mental health and suicide which they apply while carrying out follow-up calls for suicide attempts. Moreover, the DMHP in the control districts carry out monthly mental health awareness raising camps in the community to increase awareness around mental health and their services (this is not occurring in the intervention districts). The CASP team will also provide a brief training with DMHP staff in control districts covering suicide, its prevalence and associated risk factors, and myth busting around suicide prevention.

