### Training

All emergency nurses and Community Health Officers (CHOs) in the selected districts will be required to undergo CASP training, organized by the state government. The training sessions will be conducted by Master Trainers, a cadre of Rural Medical Assistants (RMAs) who will first receive a three-day training led by the study’s Principal Investigators ([name]). RMAs, trained under the Chhattisgarh RMA scheme, are formally qualified medical personnel working across Health and Wellness Centres in the state.

CHOs will participate in a two-day training program covering key topics such as understanding suicide and associated risk factors, empathetic communication, safety planning, suicide risk assessment, contact procedures, data recording, privacy and confidentiality, emergency response protocols, and self-care strategies to mitigate burnout.

Emergency nurses from all Primary Health Centres (PHCs), Community Health Centres (CHCs), and District Hospitals will undergo a one-day training delivered by Master Trainers. This training will focus on understanding suicide and its risk factors, empathetic communication, and obtaining verbal consent for study participation.

Additionally, a one-day refresher training will be provided to all health workers six months after the initial training to reinforce key concepts. Training materials will also be made available to health workers throughout the study to support their ongoing learning and implementation of CASP protocols.

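### Suicide attempts are identified through different arrangements in the two arms, so the between-arm re-attempt comparison may carry a case-finding bias of unknown direction.

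*Protocol article*

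**What the plan says.** The Study design section describes a "1:1 non-randomized, controlled pilot study", with two districts per arm.

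**CASP districts.** The Introduction says the study will train "nurses in emergency wards of health centres to identify and recruit adults who have attempted suicide from emergency wards", and places this work "in two districts where the DMHP is not providing any response to suicide attempts"; these are the two CASP districts. The Training section adds that "All emergency nurses and Community Health Officers (CHOs) in the selected districts will be required to undergo CASP training", covering nurses at primary health centres, community health centres and district hospitals. The listed content of the one-day nurse course is "understanding suicide and its risk factors, empathetic communication, and obtaining verbal consent for study participation".

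**Control districts.** The Enhanced Usual Care section says: "The CASP team will also provide a brief training with DMHP staff in control districts covering suicide". It does not mention emergency nurses. The Discussion states, without limiting it to one arm, that "nurses in emergency wards are not trained to identify and sensitively respond to attempted suicides", and concedes that "the lack of systematic data collection on suicide attempts and follow-ups in control districts complicates the evaluation". The remedy follows directly: data collectors will visit primary and community health centres weekly to improve recording and reporting at that level. District hospitals are not named, and no such visits are described for the CASP districts.

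**Analysis and baseline data.** The Data analysis section compares the percentage who re-attempt at 6 and 12 months by a Bayesian binomial test and states no adjustment. The Data collection section gives the baseline suicidality (C-SSRS) and depression (PHQ-9) scales to the intervention group only. Nurse record books hold the date, age, gender, method of attempt and consent status.

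**The concern.** Everything downstream depends on who is first recognised as having attempted suicide. Because arm equals district, a district-level difference in how cases are recognised or recorded falls entirely on the arm contrast. It acts before consent, before the first visit and before any treatment.

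If one arm's arrangements pick up a broader or a narrower range of attempts, and those attempts differ in re-attempt risk, the two percentages will differ even if CASP does nothing. A binomial test on the raw percentages cannot separate the two explanations. The C-SSRS and PHQ-9 cannot help, because control participants do not receive them at baseline. A misleading preliminary result could then inform the definitive testing that the Discussion anticipates.

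**Working it through.** **Step 1: are the arrangements different?**

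| Element | CASP districts | Control districts |
|---|---|---|
| Study training | Emergency nurses at all facility levels, and Community Health Officers | DMHP staff, brief |
| State of attempt records | Nurse record books (not limited to an arm in the text) | Conceded not to be systematic |
| Extra support for recording | None described | Weekly visits, primary and community health centres |

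The Training section does not define the selected districts. The same sentence requires Community Health Officers to take CASP training. These officers deliver CASP, so the sensible reading is the two CASP districts, as in the Introduction.

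**Step 2: how large could the effect be?** The plan gives no figure for case-finding, so there is none to reproduce. From the Sample size section I take a 10% control rate at 12 months, 250 per arm and 20% loss, which leaves 250 × 0.80 = 200 evaluable per arm. The risks and shares below are assumptions.

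Suppose low-risk and high-risk attempters have re-attempt risks rL and rH, the high-risk share in an arm is s, and CASP has no effect.

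- Rate in an arm: p = rL + (rH − rL) × s
- False difference: D = (rH − rL) × (s in control − s in CASP)
- SE = √[p₁(1 − p₁)/200 + p₂(1 − p₂)/200]
- Chance of a two-sided 5% normal test rejecting: 1 − Φ(1.96 − D/SE) + Φ(−1.96 − D/SE)

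The test is a frequentist stand-in for the planned Bayesian one. Both risk pairs match the plan's 10% when one third are high risk: 0.05 + 0.15/3 = 0.10 and 0.07 + 0.09/3 = 0.10.

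Worked row (risks 5% and 20%, shares 30% and 50%):

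- p CASP = 0.05 + 0.15 × 0.30 = 0.095
- p control = 0.05 + 0.15 × 0.50 = 0.125
- D = 0.030
- SE = √(0.095 × 0.905/200 + 0.125 × 0.875/200) = 0.0313
- D/SE = 0.96, so the chance of rejection is about 16%

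| Risks (low, high) | High-risk share, CASP v control | Rates, CASP v control | False difference (points) | Chance of rejection |
|---|---|---|---|---|
| 5%, 20% | 30% v 40% | 9.5% v 11.0% | 1.5 | 7.8% |
| 5%, 20% | 30% v 50% | 9.5% v 12.5% | 3.0 | 16% |
| 5%, 20% | 25% v 60% | 8.75% v 14.0% | 5.25 | 38% |
| 7%, 16% | 30% v 40% | 9.7% v 10.6% | 0.9 | 6.0% |
| 7%, 16% | 30% v 50% | 9.7% v 11.5% | 1.8 | 9.0% |
| 7%, 16% | 25% v 60% | 9.25% v 12.4% | 3.15 | 17% |

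Swapping the shares between arms gives the same sizes with the sign reversed, against CASP. I do not scale these against the plan's 10-point target: taken from a 10% control rate, that target means no re-attempts at all on CASP.

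**The case against.** The strongest reply is that much of the contrast is inferred. The Recruitment & Retention section has casualty nurses identify cases without naming an arm, and the record books are not limited to CASP districts. The sentence about untrained nurses is general. The control route may appear in the flowchart, which is not shown, or in a fuller protocol. District hospitals may be left out of the weekly visits because DMHP staff already follow up attempters who present to emergency wards in the control districts. The study is openly a non-randomised pilot, the comparison is secondary, and the authors disclose the problem.

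Much of this stands, and it limits the point. A reader might infer that the arms do enrol different kinds of attempters, or that trained nurses catch concealed attempts that control nurses miss, which would flatter CASP. The documents do not support either reading. No section reports case mix by arm, and recognising concealed attempts is not among the listed nurse training topics. The control districts also have an active DMHP and monthly awareness camps, which could raise disclosure there. Scenarios in which control facilities find only the obvious cases are an extreme that nothing in the article establishes.

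What survives does not rest on an omission. The stated training differs by arm, the protocol itself concedes unsystematic control data on attempts, and the stated remedy names only some facility levels. Disclosure does not correct an unadjusted comparison.

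**Conclusion.** The concern holds as a risk of bias, not as a demonstrated difference. Case identification is set up differently by arm, and the stated re-attempt analysis has no means of detecting or correcting the result. Under the assumed mixes, the false difference runs from about 1 to about 5 percentage points in either direction. That is roughly a tenth to a half of the assumed 10% control rate (0.9/10 to 5.25/10). The size rests wholly on the assumed risks and shares; the documents give neither.

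The primary outcomes that describe CASP delivery, and the progression criteria, do not use this comparison and are unaffected. The cost-utility sub-sample is drawn from the same two arms and could inherit a case-mix difference. Its models are baseline-adjusted, and I have not sized that effect. This is a worthwhile, inexpensive improvement to a secondary comparison.

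**What to change.** **Remaining recruitment.** Use one written case definition and the same nurse record book in all four districts, district hospitals included. Have data collectors check facility records in the same way in both arms. Record the date of the change so that participants enrolled before and after it can be told apart.

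**Before the re-attempt comparison.** Tabulate by district and arm the number of attempts identified, facility level, method of attempt, age and gender. Add an analysis of re-attempt adjusted for these items, and state that the between-arm difference may partly reflect case-finding. Keep the adjustment small: at 10% in 400 evaluable participants there would be about 40 events.

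I would not restrict the main comparison to facility or method strata found in both arms. Choosing strata after seeing the data is debatable, and selection within a method would remain. For the same reason, adjustment reduces the problem only as far as the recorded items capture it.

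**Cost.** Some data-collector time in the CASP districts and a mid-study change in recording. The Study status section reports recruitment as ongoing, with data collection ending in November 2025. Participants with a full 12 months of follow-up must therefore have enrolled by about November 2024, and the recruitment change helps only those not yet enrolled. The table, the adjusted analysis and the caveat remain possible whatever the recruitment stage, as far as the control records allow.

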## Conclusion

The knowledge generated through this study will inform the future testing and scale-up of CASP across Chhattisgarh and other regions in India where specialist care and targeted suicide prevention initiatives are minimal. By examining factors influencing the successful implementation of CASP in public health systems, this study will support researchers, health professionals, and policymakers in addressing the suicide prevention gap in low-resource settings. It offers a crucial step toward reducing repeat suicide attempts and enhancing community-level responses to suicide in LMICs.

## Ethics and consent

Ethical approval has been obtained from Indian Law Society’s Institutional review board (ILS/173B/2022) dated 26 September 2022, the University of Utrecht Ethical Review Board, Netherlands (#23-0003) dated 1 October 2022 and the Clinical Trials Registry India (CTRI) (CTRI/2022/12/048087) for this study. All procedures will be done in adherence to guidelines outlined in the Declaration of Helsinki, including obtaining written informed consent from participants, ensuring confidentiality, and protecting participants’ rights, privacy and well-being. Written consent will be collected by Community Health Officers in the intervention districts and by data collectors in the control districts. Authorship of any publications which emerge from this project will be agreed upon by all authors based on individual contribution to the manuscript, project implementation, concept, steering, and evaluation.

